## Methods/Design

### Aim

The aim of the study is to determine the efficacy of elective manual rotation in the management of OP position in the second stage of labour.

### Hypothesis

Among women who are at least 37 weeks gestation and whose baby is in the OP position early in the second stage of labour, manual rotation compared with a ‘sham’ rotation will result in a reduction in operative delivery.

### Primary objectives

The primary objectives are to determine the differences between intervention and control groups in the operative delivery rate (defined as vacuum, forceps and/or caesarean section deliveries).

### Secondary objectives

The secondary objectives are to determine the differences between intervention and control groups in caesarean section, in the combined measure of serious maternal morbidity and mortality within six weeks of birth, and in the combined measure of serious perinatal/neonatal morbidity and mortality within six weeks of birth.

### Trial design

The POP-OUT trial is designed as a superiority, double-blinded, multicentre, randomised controlled clinical trial with two parallel groups and a primary endpoint of operative delivery. Randomization will be performed as block randomization with a 1:1 allocation.

### Eligibility criteria

#### Inclusion criteria

Inclusion criteria include the following:age ≥ 18 yearssingleton pregnancy≥37 weeks of gestationplanned vaginal birthcephalic presentationfull cervical dilatationocciput posterior position confirmed by ultrasound where the occiput is <45° from the midline

#### Exclusion criteria

Most exclusion criteria were selected on the basis of predisposition to requiring an operative delivery and are as follow:clinical suspicion of cephalopelvic disproportionprevious caesarean sectionbrow or face presentation‘Pathologic’ CTG according to RCOG classification plus either baseline >160 beats per minute or reduced variabilityfetal scalp pH <7.25 or lactate >4known or suspected chorioamnionitisintrapartum haemorrhage >50 mLtemperature ≥38.0°C in labourpre-existing maternal diabetes suspected fetal bleeding disorder (theoretical risks associated with procedures involving manipulation of fetal position) known major anatomical fetal abnormality (could influence safety or efficacy of manual rotation).

### Eligibility criteria for study centres

Ability to provide a 24-hour on-call service with experienced operators to perform the intervention.

### Individuals who will perform the intervention

Only obstetricians or midwives who are experienced in performing a manual rotation and have performed at least 20 procedures will participate in the study. All operators will complete a questionnaire outlining their technique and experience.

### Intervention: manual rotation

#### Intervention description

Manual rotation is performed at full dilatation if the fetal position is OP. The technique employed will be at the discretion of the operator performing the procedure.

With the membranes ruptured, a vaginal examination is performed and the woman is asked to bear down. Constant pressure is exerted with the index finger against the lambdoid suture to rotate fetal head. This may take 2 to 3 contractions and the position is commonly held for two contractions while the woman bears down to reduce the risk of reverting back to the OP position.

Alternatively, the examiner places two fingers behind the fetal ear or the entire hand behind the occiput and applies constant flexion and rotation to the fetal head.

For purposes of the POP-OUT Trial, the procedure will be described as a ‘manual rotation (digital)’ if only the fingers are used and as a ‘manual rotation (whole hand)’ if the whole hand is used.

### Comparator: sham procedure

#### Comparator description

Women randomized to the ‘sham rotation’ will have the same apparent vaginal examination as the intervention but no rotational force will be applied. The woman is asked to bear down. The accoucheur places fingers in the vagina over 5 contractions as if s/he were performing a manual rotation.

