### Criteria for discontinuing or modifying the intervention

The intervention or sham will be discontinued if there is a clinical necessity or at the request of the participant. This could occur if there is evidence of fetal compromise necessitating emergent delivery or if the participant is in significant discomfort.

Each operator will complete a data collection form at the time of the procedure or sham, which will describe in detail what was done. Adherence with treatment allocation will be monitored by comparing these datasheets with the computer randomisation records.

All interventions and usual care provided by doctors and midwives looking after the participant will be allowed. However, if the doctor is intending to perform an operative delivery or a manual rotation, the woman will not be randomised. Data will be collected about use and timing of any manual rotations performed by the participant’s carers.

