### Randomization/allocation concealment

Randomization will be stratified by parity, hospital site and epidural due to the potentially strong association between operative delivery (the primary outcome) and each of these factors. Randomization will be centrally controlled using computerized sequence generation, which can be accessed 24 hours per day using a toll-free telephone line.

In order to reduce the risk of randomising an ineligible participant, randomisation will occur immediately before the intervention or sham procedure is to be performed. An example of a participant becoming ineligible would be if the fetus rotated from the occiput posterior to occiput transverse position. Each investigator will complete a data collection form at the time the manual rotation or sham procedure is performed outlining the treatment allocation, clinical findings, and whether or not the fetus was successfully rotated.

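### The subgroup by rotation technique rests on what was done after allocation, and only in women who were rotated, so it has no like-for-like controls

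*Protocol article*

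**What the plan says.** All places are in the protocol article.

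- **Choice of technique** (Intervention description): "The technique employed will be at the discretion of the operator performing the procedure". Besides pressure with the index finger, the examiner may place "two fingers behind the fetal ear or the entire hand behind the occiput".
- **Labels** (same section): a rotation is digital "if only the fingers are used" and whole hand if the whole hand is used. Both labels are worded for manual rotations.
- **Sham** (Comparator description): "the same apparent vaginal examination as the intervention", without rotational force. "The accoucheur places fingers in the vagina over 5 contractions as if s/he were performing a manual rotation".
- **Who knows the allocation, and when** (Randomization/allocation concealment; Study conduct): randomisation comes immediately before the procedure. The study investigator randomises the woman and keeps the allocation sheet.
- **What is recorded about technique**: per operator, "All operators will complete a questionnaire outlining their technique and experience" (Individuals who will perform the intervention). Per woman, "Each operator will complete a data collection form at the time of the procedure or sham, which will describe in detail what was done" (Criteria for discontinuing or modifying the intervention), and likewise "Each investigator will complete a data collection form at the time the manual rotation or sham procedure is performed outlining the treatment allocation" (Randomization/allocation concealment).
- **Subgroup** (Analysis): by the technique used for the manual rotation, whole hand against fingers.

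**The concern.** A subgroup analysis in a randomised trial is protected by randomisation only if each woman's subgroup could have been known without knowing her arm. Here membership depends on what the operator did once the arm was known, and the labels exist for one arm. A woman in the sham arm who would have had a whole-hand rotation cannot be identified, so whole-hand rotations have no randomised whole-hand controls.

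The labels add a second problem. A rotation that starts with fingers and ends with the whole hand is no longer fingers only, so it counts as whole hand. If operators switch when fingers fail, difficult cases move out of the digital group and into the whole-hand group.

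At stake is the reading of the technique result. A reader could conclude that one technique works better, and change practice or training, when the difference reflects which women received it.

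**Working it through.** **Step 1. Is technique fixed for each woman before allocation?** Three records could do this.

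- The operator questionnaire describes the operator, not the woman. The article does not tie it to the subgroup.
- The data form is completed at the procedure or sham and describes what was done, so it follows allocation.
- The pre-procedure data sheet (Study conduct) holds the second ultrasound, which comes before randomisation. The article lists no intended technique on it.

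Nothing shown fixes technique for each woman beforehand.

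**Step 2. Can the bias be sized?** Only under assumptions. From Sample size: 68% operative delivery with sham, 50% with rotation, an effect of 18 points. Not in the article, so assumed:

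- w = share of rotations planned as whole hand, 20–50%
- s = share that switch from fingers to whole hand after fingers fail, 10–30%
- switchers have the control rate of 68%, women planned as whole hand have 50%, and the rotation arm as a whole has 50%

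There is no true technique effect in this set-up. Grouped by technique used:

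- whole-hand rate = 0.50 + 0.18s/(w + s)
- digital rate = 0.50 − 0.18s/(1 − w − s)
- gap = 0.18s / [(w + s)(1 − w − s)]

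| s | w = 20% | w = 30% | w = 40% | w = 50% |
|---|---|---|---|---|
| 10% | 8.6 | 7.5 | 7.2 | 7.5 |
| 20% | 15.0 | 14.4 | 15.0 | 17.1 |
| 30% | 21.6 | 22.5 | 25.7 | 33.8 |

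(Gap in percentage points.)

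Against all shams, with w = s = 20%: whole hand 0.50 + 0.036/0.40 = 59%, a difference of −9 points; digital 0.50 − 0.036/0.60 = 44%, a difference of −24 points. The true effect is −18 in both.

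Grouped by intended technique, the same women show no gap. Those planned as whole hand are at 50%. Those planned as digital, switchers included, are at (0.50 − 0.50w)/(1 − w) = 50%. The whole gap comes from how the groups are formed.

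**Step 3. What could a corrected subgroup show?** Approximate 95% half-width of a risk difference with n women per arm: 1.96 × √[(0.68 × 0.32 + 0.50 × 0.50)/n] = 1.96 × √(0.4676/n).

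*Usual technique, all 254 women, 127 per arm, assumed whole-hand share 20–50%:*

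- n = 25.4 gives 26.6 points; n = 63.5 gives 16.8 points.
- The difference between the two subgroup effects: 1.96 × √(0.4676/25.4 + 0.4676/101.6) = 29.7 points at 20%, and 1.96 × √(2 × 0.4676/63.5) = 23.8 points at 50%.

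*Intended technique, women still to be randomised:* Trial status gives 160 recruited. If all 160 were randomised, 254 − 160 = 94 remain, or 47 per arm. Then n = 9.4 gives 43.7 points and n = 23.5 gives 27.6 points.

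**The case against.** **The article does not say how shams enter the subgroup, and the form covers shams.** True: hand use in shams may well be recorded, and the form of the comparison can be left to an analysis plan. But that record is also made after allocation. It shows how the sham was imitated, not how the woman would have been rotated. The article itself fixes the grouping variable as technique used, and a later plan cannot recover an intention that was never written down.

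**The bias figures rest on invented inputs.** This stands. The results in Step 2 move fourfold or more across plausible inputs, and would change again if no operator ever planned a whole-hand rotation. They show that the bias can be material; they do not estimate it.

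**The remedy buys little precision.** This also stands. The argument for it is validity and honest labelling, not power.

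**A stronger reading is tempting: that the sham is fingers only, does not match whole-hand rotations, and so undermines masking.** A reader might infer this from the word fingers. The text does not support it. The governing sentence asks for the same apparent examination, done as if rotating. Five contractions agree with the intervention's two to three to rotate plus two to hold. The sham text does not say fingers alone, whereas the digital label does. A whole-hand sham would also mean possible extra discomfort without benefit, so its absence would be a trade-off rather than a mistake.

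**A reader might also fault the masking check for asking only the carer to guess.** The article names carers' behaviour as a route for performance bias (Explanation for choice of comparator). Asking the woman too is a preference, not the correction of an error.

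**Conclusion.** The point holds for the technique subgroup. As written, it is defined after randomisation and only among rotated women, and the labels move switched cases into the whole-hand group. Neither a comparison between techniques nor a comparison of each with all shams would isolate the effect of technique.

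The size is unknown: the article gives no switching rate, no whole-hand share and no outcome for switched cases. The range of about 7 to 34 points holds only under the assumptions in Step 2.

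The primary comparison by allocated arm does not use technique and is unaffected. This is a point to consider, not a threat to the trial's main result.

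**What to change.** 1. In Analysis, define the technique subgroup in both arms by the operator's usual technique (digital or whole hand) from the planned questionnaire, provided it was completed before that operator's first trial procedure.
2. For women not yet randomised, also record the intended technique on the existing pre-procedure data sheet before the randomisation call. The operator stays free to switch, and the technique used is still recorded.
3. Test the treatment-by-technique interaction, separately for each definition, without merging the two into one variable.
4. Keep any analysis by technique used, labelled non-randomised and descriptive. Present the whole as exploratory.

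**Cost.** One extra field and a small ethics amendment; no change to sample size. For women already randomised only the operator-level proxy exists, and it will misclassify operators who use both techniques. If the 160 recruited are all randomised, intended technique can cover at most 94 of 254 women (37%); the article does not say whether recruited means consented or randomised. If even the extra field is unwelcome, items 1, 3 and 4 need only a change of wording and use of the questionnaire already planned.

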### The timing of the intervention

The intervention will begin once full dilatation has been diagnosed and the woman has the first urge to push or after one hour, whichever occurs first.

### Criteria for discontinuing or modifying the intervention

The intervention or sham will be discontinued if there is a clinical necessity or at the request of the participant. This could occur if there is evidence of fetal compromise necessitating emergent delivery or if the participant is in significant discomfort.

Each operator will complete a data collection form at the time of the procedure or sham, which will describe in detail what was done. Adherence with treatment allocation will be monitored by comparing these datasheets with the computer randomisation records.

All interventions and usual care provided by doctors and midwives looking after the participant will be allowed. However, if the doctor is intending to perform an operative delivery or a manual rotation, the woman will not be randomised. Data will be collected about use and timing of any manual rotations performed by the participant’s carers.

### Outcomes

#### Primary outcome

The primary outcome will be operative delivery (vacuum, forceps and/or caesarean section).

#### Secondary outcomes

Secondary outcomes will include the following:Caesarean section (reported as proportion of participants who had a caesarean section) andSerious maternal morbidity or mortality (combined outcome), which includes the following: post-partum haemorrhage requiring blood transfusion, third or fourth degree perineal trauma; dilatation and curettage for bleeding or retained placental tissue; cervical laceration; vertical uterine incision; vulvar or perineal haematoma; pneumonia; venous thromboembolism requiring anticoagulation; wound infection requiring hospital stay more than 7 days; readmission to hospital for obstetric-related causes; wound dehiscence; maternal fever of at least 38.5°C on two occasions at least 24 hours apart not including the first 24 hours; bladder, ureter or bowel injury requiring repair; genital-tract fistula; bowel obstruction; or admission to intensive care unit. This will be reported as a proportion of participants with serious morbidity or mortality.Serious perinatal/neonatal morbidity or mortality within 6 weeks of birth (combined outcome), which will include the following: shoulder dystocia requiring manouvres other than McRoberts/suprapubic pressure or resulting in neonatal injury, 5-minute Apgars < 4; arterial cord pH <7.0 or lactate >10 or base excess < −15; seizures < 24 hours of age, intubation/ventilation >24 hours, tube feeding >4 days, admission to neonatal intensive care >4 days, neonatal jaundice requiring phototherapy, neonatal fracture, intraventricular/intracranial haemorrhage, subgaleal haemorrhage, neonatal blood transfusion, hypoxic ischaemic encephalopathy, or neuropraxia. This will be reported as a proportion of participants with serious morbidity or mortality.

#### Other outcomes

Other outcomes will be assessed during delivery admission and at t 6-weeks, 6-months, and 1-year postpartum.

The following outcomes will be assessed during delivery admission:length of second stage (median)time from intervention or sham until delivery (median)estimated blood loss at delivery (median: visual estimation by midwife or doctor)any perineal/vaginal trauma requiring suturing (proportion)length of hospital stay (median)

The following outcomes will be assessed at 6 weeks:still breast feeding (proportion)satisfaction with birth (VAS scale) (median)saw a health professional for depression since delivery (proportion)health-related quality of life (SF-12) (median)

The following outcomes will be assessed at 6 months:still breast feeding (proportion)saw a health professional for depression since delivery (proportion)health-related quality of life (SF-12) (median)

The following outcomes will be assessed at one year:still breast feeding (proportion)saw a health professional for depression since delivery (proportion)health-related quality of life (SF-12) (median)pelvic floor function (bowel, urinary, prolapse, and sexual function domains - using the Australian pelvic floor function questionnaire [34] (medians)

### Sample size

The sample size (254) was calculated on the basis of the primary outcome. The power calculation was based on our prospective cohort study of 160 women that was completed in May 2009 [3] and showed an operative delivery rate of 68% in the OP group, and from our survey of obstetricians conducted in 2010, who indicated they would perform a manual rotation for OP position if it reduced the rate of operative delivery from 68% to 50% [10]. To detect a reduction in the rate of operative delivery from 68% in the control group to 50% in the intervention group, a sample size of 127 women in each group (total = 254) will be required to have 80% power of finding a result. Alpha = 0.05 (2-tailed), Beta = 0.20 (Epi-Info version 3.3.2).

### Randomization/allocation concealment

Randomization will be stratified by parity, hospital site and epidural due to the potentially strong association between operative delivery (the primary outcome) and each of these factors. Randomization will be centrally controlled using computerized sequence generation, which can be accessed 24 hours per day using a toll-free telephone line.

In order to reduce the risk of randomising an ineligible participant, randomisation will occur immediately before the intervention or sham procedure is to be performed. An example of a participant becoming ineligible would be if the fetus rotated from the occiput posterior to occiput transverse position. Each investigator will complete a data collection form at the time the manual rotation or sham procedure is performed outlining the treatment allocation, clinical findings, and whether or not the fetus was successfully rotated.

### Blinding

The following groups will be masked:The participantsThe clinicians caring for the participant (including doctors and midwives)The data collectorsThe statisticians who will perform the analysis

### Unblinding

Unblinding will occur if the clinician requests it on the basis of clinical need or if the participant insists.

### Data collection, management and analysis

#### Study conduct

Consent will occur at three possible time points Figure 1:

**Figure 1 Fig1:**
[figure not shown]
**An overview of the conduct of the POP-OUT Trial.**

AntenatallyIn the latent phase of labourIn the active phase of the first stage of labour, with an effective epidural anaesthesia

An ultrasound will be performed at full dilatation by the clinician caring for the woman and the findings will be recorded on a data sheet immediately afterwards.

An hour after full dilatation or at the first urge to push, a study investigator (with no clinical responsibility for the woman in the trial) will confirm the OP position by a second (pre-procedure) bedside ultrasound. If the fetal position is still OP and the woman still wishes to participate, then the study investigator will randomise the woman to either manual or sham rotation. The treatment allocation will be recorded on a randomisation sheet that the investigator will keep on their person and not show to any of the participant’s carers.

After the manual rotation or sham has been performed the ultrasound will be repeated, ensuring that the woman and her carers do not see the screen. The investigator will leave and the woman will have her usual care from this point onwards. The investigator will record the findings of the vaginal examination he/she performed before the procedure, details of the procedure and post-procedure ultrasound findings on the same data sheet as the pre-procedure ultrasound. The study investigator will also keep this data sheet on their person and not show it to any of the participants’ carers.

### Consent

Participants will be provided with written information via information pamphlets, posters and the trial website. Informed consent will be obtained by research midwives or midwives/medical staff involved in potential participants’ care (Figure 1, Table 2). A detailed information sheet will be provided to all participants. Participants will be informed of the potential risks of manual rotation, including umbilical cord prolapse, given the opportunity to ask questions and informed that they have the right to change their mind at any time.

**Table 2 Tab2:** **The POP-OUT study time-line for the schedule of enrolment, allocation and follow-up**

	**Enrolment**		**Allocation**		**Post-allocation**			
**Timepoint**	**35-37 wks gestation**	**1** ^**st**^ **stage labour**	**During 2nd stage of labour**	**Immediately after allocation**	**1-3 days**	**6 wks**	**6 mths**	**12 mths**
1^st^ Eligibility screen	X							
2^nd^ eligibility screen		X						
Informed consent	X	X						
Allocation			X					
Intervention				X				
